#### Sample size consideration for each test separately

Published sensitivity for F-DG-PET for the characterisation of SPN vary between 77 and 96% (pooled weighted average: 92%) and specificity varies between 76 and 100% (pooled weighted average: 90%). Published sensitivity and specificity values for DCE-CT vary between 81 and 100% (pooled weighted average: 87%) and 29 and 100% (pooled weighted average: 83%) respectively. Based on two previous UK studies, the mean prevalence of malignancy in indeterminate SPN has been reported as 68.5% [18]. At this prevalence, a sample size of 375 will produce approximately 257 malignant and 118 benign SPNs. This will give confidence limits for sensitivity and specificity of DCE-CT of 87% +/- 4.1% and 83% +/- 6.8% respectively, with sensitivity and specificity values for F-DG-PET of 92% +/- 3.3% and 90% +/- 5.4% respectively. These estimates will provide sufficiently narrow confidence limits to allow precise economic modelling based on the results. For the purposes of economic analyses, we will also consider combining our data with the meta-analysis results from our systematic review (section 8.2), where previous studies we currently know about total 217 patients who had undergone both techniques [8-10]. Recruitment rates are anticipated to be high (70%) because DCE-CT will be additional rather than an alternative to normal care, and is readily incorporated into the existing PET-CT examination. We expect to recruit the required sample size (375) in 18 months. With a 70% recruitment percentage of all meeting the inclusion criteria, in order to recruit 375 patients we need to invite  $375/0.7 = 536$  patients.

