### Statistical analysis

#### (i) Diagnostic accuracy for 2 year follow-up

We will consider the diagnostic accuracy of positive FDG-PET and DCE-CT, both separately and in conjunction, in relation to a diagnosis of lung cancer by 2 years. In these analyses we will only be able to use those patients for whom the presence of lung cancer by 2 years is known; i.e. those without diagnosed lung cancer who drop-out before the end of 2 years will be excluded. This is likely to be small.

Initially, the separate diagnostic performance of FDG-PET/CT and DCE-CT will be examined using diagnostic criteria defined and over the full range of possible threshold values. At each threshold sensitivity and specificity will be estimated (with 95% confidence intervals), and the Receiver Operator Characteristic (ROC) curve will be calculated. The optimal cut-point from the range of values will be reported based on keeping the sensitivity above 90% and maximising specificity within this limitation. An alternative cut-point that provides the best trade off in sensitivity and specificity will also be reported. The sensitivity, specificity, positive predictive value (PPV) and negative predictive value (NPV) at these cut-points will then be presented with 95% confidence intervals. When translating sensitivity and specificity to PPV and NPV, we will need to assume a particular prevalence. This will be based on the prevalence in our study, and also we will report PPV and NPV for a range of other prevalence's reported in the literature (identified from our systematic review).

Secondly, the diagnostic performance of FDG-PET/CT and DCE-CT combined will also be examined using the same techniques as above; we will class patients as 'positive' if they have both FDG-PET and DCE-CT positive, and all others as 'negative'. Again, a range of different thresholds for both FDG and DCE will be considered.

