Thirdly, a logistic regression model will be considered including both PET and CT, on their original scale, as covariates. This may increase the power and diagnostic accuracy of identifying those who will subsequently be diagnosed with lung cancer. It will provide a risk score and predicted probability of lung cancer for each individual, based on their specific test values. We will then use a cut-off value to decide when a risk score is high (such that we predict an adverse outcome) and when it is low (such that we predict a good outcome). The calibration of the model will be assessed by grouping patients into deciles ordered by predicted risk and considering the agreement between the mean predicted risk and the observed number of true lung cancer cases in each decile (sometimes referred to as the expected versus observed statistic, E/O). The derived diagnostic rule will be cross validated by comparing the classification of each patient with their actual primary outcome of confirmed lung cancer, allowing an estimate of the sensitivity and specificity of the prediction model. Then, by varying the chosen cut-off level, we will produce a receiver operating characteristic (ROC) curve summarising the sensitivity and specificity of the predictive rule across the range of cut-offs. The overall discriminatory ability will be summarised as the Area Under ROC curve (AUC) with 95% confidence interval. The most suitable cut-off level can then also be detected. The internal validity of the final model will also be assessed by the bootstrap re-sampling technique to adjust for over-optimism in the estimation of model performance due to validation in the same dataset that was used to develop the model itself.

If the above methods all show poor accuracy performance (in terms of calibration and/or discrimination), then the logistic regression model will be extended to include additional patient-level covariates (such as time from FDG injection to PET-CT scan), in addition to test results. Demographic information will be considered here as well as clinical and imaging features considered indicative of a higher likelihood of SPN malignancy than unselected patients. The performance of the model will also be evaluated at the

practice-level where possible, to ascertain whether model performance is consistent in each practice or, if not, the variability in performance across practices, and whether it can be improved by tailoring the prevalence used in each practice.

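### Cut-points are chosen and evaluated on the same patients without the optimism correction that the regression models get, and no DCE-CT positivity threshold is fixed in advance

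*Protocol*

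**What the plan says.** Protocol section 9.1, Statistical analysis (i), examines each test at defined criteria and across every possible threshold. One cut-point is selected "based on keeping the sensitivity above 90% and maximising specificity within this limitation". A second is the one with the best trade-off between sensitivity and specificity; how trade-off is measured is not said. Sensitivity, specificity, PPV and NPV "at these cut-points will then be presented with 95% confidence intervals". The same techniques are applied to the rule that calls a patient positive only if both tests are positive, where "a range of different thresholds for both FDG and DCE will be considered".

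The next step, a logistic model on both tests, does get a correction: "The internal validity of the final model will also be assessed by the bootstrap re-sampling technique", with the stated aim of adjusting for over-optimism. Part (ii) plans bootstrapping and shrinkage for the survival model, if appropriate. Neither is extended to the threshold searches.

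Fixed criteria exist in part. Section 8.1 sets positivity rules for PET combined with CT appearances. Section 1.1 mentions an SUV above 2.5, but only as background. For DCE-CT, section 8.2 refers only to measurements of contrast enhancement, and Appendix 3 covers acquisition and measurement. Neither gives a positivity value.

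The sample size text says the expected intervals give "sufficiently narrow confidence limits to allow precise economic modelling based on the results".

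**The concern.** A cut-point that is the best of many on one data set tends to look better there than in new patients, and the more thresholds are searched, the larger the gap. An interval computed as if the cut-point had been given in advance also leaves out the uncertainty in the cut-point itself.

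The protocol recognises this for its regression models and leaves the threshold searches uncorrected. DCE-CT, the test under evaluation, has no pre-stated threshold to fall back on.

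Two things are at stake. Sections 2 and 3.1 compare combined testing with either test alone, and the combination is searched over two thresholds while a single test is searched over one. Accuracy estimates also feed the economic model in section 8.7, and any data-chosen cut-point used there would carry its optimism and its too-narrow interval along.

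**Working it through.** **Inputs.** Section 9.1 states that "a sample size of 375 will produce approximately 257 malignant and 118 benign SPNs", because "the mean prevalence of malignancy in indeterminate SPN has been reported as 68.5"% (0.685 × 375 = 257). Planning accuracies are 87%/83% for DCE-CT and 92%/90% for PET.

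**The plan's own precision.** It gives "confidence limits for sensitivity and specificity of DCE-CT of 87% +/- 4.1% and 83% +/- 6.8% respectively", and ±3.3% and ±5.4% for PET. With half-width 1.96 × √(p(1−p)/n):

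- DCE-CT sensitivity: 1.96 × √(0.87 × 0.13/257) = 4.1 points
- DCE-CT specificity: 1.96 × √(0.83 × 0.17/118) = 6.8 points
- PET sensitivity: 1.96 × √(0.92 × 0.08/257) = 3.3 points
- PET specificity: 1.96 × √(0.90 × 0.10/118) = 5.4 points

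All four reproduce. They are plain binomial limits at a fixed threshold.

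**Assumptions beyond the protocol.** The protocol gives no distribution of test values, so I took equal-variance normal scores in each class, passing through the planning accuracies. The separations are z(0.87) + z(0.83) = 2.08 for DCE-CT and z(0.92) + z(0.90) = 2.69 for PET. Best trade-off is read as the maximum of sensitivity + specificity. Intervals are Wilson. There were 8,000 simulated trials per single-test scenario and 1,500 for the combined rule, with within-class correlation 0.3.

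**(a) Best trade-off cut-point, one test.**

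| | Apparent sens. | True sens. | Apparent spec. | True spec. | Joint coverage |
|---|---|---|---|---|---|
| DCE-CT | 85.8% | 84.7% | 86.5% | 84.6% | 87% |
| PET | 91.7% | 90.7% | 92.2% | 90.7% | 88% |

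Overstatement is 1.1 and 1.9 points for DCE-CT, and 0.9 and 1.5 for PET. Each interval alone covers 93–94%. Two independent 95% intervals would jointly cover 0.95² = 90%.

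**(b) Both-positive rule, two thresholds, sensitivity above 90%.** Apparent sensitivity is 91.0% against a true 89.9% (+1.1), and apparent specificity 94.6% against 92.6% (+2.0). Joint coverage is 85%. A coarser grid of thresholds gives about 1 point of specificity optimism instead of 2. Under the same rule a single test shows +0.4 points in sensitivity and about 0 in specificity, so the bias differs between the strategies being compared.

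**(c) Rule of sensitivity above 90%, one test.** Apparent sensitivity is 90.3% against a true 89.9%. Specificity is unbiased, and both intervals cover about 95% at the cut-off actually chosen. True sensitivity at that cut-off is below 90% in about 50% of trials for both tests.

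The result changes if the interval is read as specificity at the point of 90% sensitivity. For DCE-CT that specificity is Φ(2.08 − 1.28) = 78.8%. Its binomial SE is √(0.788 × 0.212/118) = 3.8 points. Estimating the cut-point adds the ratio of the two densities there, φ(0.80)/φ(1.28) = 1.65, times √(0.9 × 0.1/257) = 1.87 points, which is 3.1 points. The total is √(3.8² + 3.1²) = 4.9 points; the simulated SD is 4.8. The binomial interval then covers 86–87% in simulation. For PET the binomial SE is 2.5 points against a simulated SD of 3.0, and coverage is 92%.

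**Check of the remedy** (400 trials × 200 bootstraps, cut-point re-selected in each resample). At the best trade-off, DCE-CT specificity is 86.4% apparent, 85.0% corrected and 84.5% true. For PET it is 92.2%, 91.1% and 90.6%. For specificity at 90% sensitivity, the half-width rises from 7.4 to 9.6 points (DCE-CT) and from 4.9 to 5.9 (PET), and coverage returns to about 94%.

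**The case against.** The strongest reply is that the most explicit rule, sensitivity above 90%, behaves well on a single test. A reader might infer that its intervals are invalid, or that the reported sensitivity tells nothing about the chosen cut-off. Part (c) shows otherwise: optimism is 0.4 points or less and coverage at that cut-off is nominal. The interval around an observed 90% also shows the reader that the true value may be lower. What stands is narrower: a cut-point presented as keeping sensitivity above 90% does so only about half the time, and the shortfall in coverage concerns a different target, specificity at exactly 90% sensitivity. That shortfall is clearly larger for DCE-CT than for PET.

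A reader might also infer that the data-chosen cut-points are the primary results and the inputs to the economic model. The protocol does not say so. Section 3.1 names sensitivity, specificity and accuracy without tying them to a threshold, section 9.1 also uses defined criteria, and section 8.1 fixes rules for PET with CT appearances. The economic analysis varies accuracy in sensitivity analyses, and section 9.1 considers pooling with the meta-analysis. This limits the reach of the point, but it does not supply a criterion for DCE-CT.

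Finally, no interval method is named, and one could be set in an analysis plan that is not shown. That is fair as to method. But the protocol itself fixes selection and reporting on the same patients and names a correction for the models alone, so the point does not rest on a missing detail.

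**Conclusion.** The point holds, at modest size. The best trade-off cut-point overstates sensitivity by about 1 point and specificity by 1.5 to 2, with joint coverage of 87–88% against about 90%. The two-threshold rule overstates sensitivity by about 1 point and specificity by about 1 to 2, and so tilts the comparison towards combined testing. Section 9.1 powers its comparison of joint testing with PET for a 4-point loss in sensitivity, so a tilt of this order is not negligible. For the 90% rule on one test, the defect is confined to the label of sensitivity above 90% and to any reading of the interval as specificity at that operating point.

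These sizes depend on binormal scores, the assumed correlation, the fineness of the threshold grid, the planned 257/118 split and the reading of best trade-off as maximum sensitivity + specificity. That the intervals would be plain binomial is an inference from the sample size section. The optimism is smaller than the planned half-widths of 3.3 to 6.8 points. It warrants a change because the remedy is cheap and the protocol already uses it elsewhere.

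**What to change.** In section 9.1, state one DCE-CT enhancement criterion and one PET criterion before outcome data are seen, and make accuracy at these the main result. The choice of values is for the investigators.

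Label cut-points chosen on the trial data as exploratory, and define best trade-off. Extend the bootstrap already planned for the logistic model to the whole cut-point search, repeating the selection in every resample and including the two-threshold search for the combined rule. Report optimism-corrected sensitivity, specificity, PPV and NPV with bootstrap intervals, and use these wherever a data-chosen cut-point enters the economic model or the comparison of combined with single testing.

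The cost is protocol or SAP wording and some analysis code, with no extra patients or scans. Estimates become slightly less favourable and intervals wider.

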(ii) Flexible parametric analysis for lung cancer risk including those who drop-out before 2 years

To include any censored observations (i.e. those who were lost to follow-up before the end of 2 years and had not been diagnosed with lung cancer) a survival analysis will also be considered. This will account for the length of follow-up for each individual (regardless of their length of follow-up), and the exact time of their lung cancer diagnosis or censoring point. Kaplan-Meier plots will, if appropriate, be presented with log-rank tests to compare between the positive and negative diagnoses. In addition, we will use a flexible parametric survival analysis [29,30], that flexibly models the baseline hazard using restricted cubic splines, and computes hazard ratios for each test (on their continuous or dichotomised scale, as included), which are very similar to those from a Cox regression (which does not provide the baseline hazard though). Using the baseline hazard and hazard ratios from the fitted model – in a similar manner to the logistic regression approach described above – this will produce a risk score and a probability of being diagnosed with lung cancer by 2 years for individuals with a particular test values (or combination of test values). Calibration and discrimination of the model at 2 years of follow-up can then be checked back at the individual level. For example, for each patient their own predicted probability of being diagnosed with lung cancer by 2 years will be available from the model. Then, for each decile of predicted risk, the expected (E) probability of lung cancer will be compared with the observed (O) probability of lung cancer as obtained from a Kaplan-Meier curve of the patients in that decile. In each decile, the E/O statistic should be close to 1 if the performance of the model is consistently good across deciles. In other words, the calibration slope should be 1. The C statistic will also be calculated to examine discrimination. Bootstrapping and shrinkage methods will be used, if appropriate, to reduce over-optimism from developing and validating the model on the same set of observations. Finally, the performance of the model will be evaluated at the practice-level where possible, to ascertain whether model performance is consistent in each practice or, if not, the variability in performance across practices.

Interim analysis and data storage

No interim analysis is planned for this study

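### The decile E/O standard for calibration breaks down in the lowest-risk deciles even for a well-calibrated model, and it is wrongly equated with a calibration slope of 1

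*Protocol*

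**What the plan says.** Section 9.1(i) plans a logistic model with both test values as covariates. On calibration it states: "The calibration of the model will be assessed by grouping patients into deciles ordered by predicted risk". Mean predicted risk is then set against the observed cancers in each group, and the protocol names this the E/O statistic. It gives no numerical standard there.

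Section 9.1(ii) plans a flexible parametric survival model and checks it at 2 years in the same way, with the observed side taken from a Kaplan-Meier curve within the decile: "for each decile of predicted risk, the expected (E) probability of lung cancer will be compared with the observed (O) probability". Here a standard is given: "In each decile, the E/O statistic should be close to 1 if the performance of the model is consistently good across deciles". It is followed by: "In other words, the calibration slope should be 1". No tolerance, interval or rule for a decile with no observed cancer accompanies it.

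On optimism, 9.1(i) says: "The internal validity of the final model will also be assessed by the bootstrap re-sampling technique to adjust for over-optimism". Section 9.1(ii) plans bootstrapping and shrinkage only where judged appropriate. Neither part says which performance measures are corrected.

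**The concern.** A ratio with the observed count in its denominator behaves badly where events are few. Accurate tests push the cancers into the upper deciles and leave the lowest ones nearly empty. The better the model, the less computable the stated measure becomes at the low-risk end.

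A sound model could then be reported as poorly calibrated among low-risk nodules, or the reader could be shown an empty cell. Low predicted risk is the range in which a benign imaging result might be relied on, so a readable check matters there.

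The second problem is the equivalence. Someone following the text could report a slope of 1 as proof that the decile ratios are sound, or the reverse. A slope estimated in the development data would be offered as evidence when it carries almost none.

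**Working it through.** **Inputs.** From section 9.1, sample size for each test separately: N = 375, prevalence 0.685, PET sensitivity/specificity 92/90%, DCE-CT 87/83%. Assumed, because the protocol does not give them: normal markers with equal variance in malignant and benign nodules, separated by z(sensitivity) + z(specificity); within-group correlation 0.3 to 0.6; and a band of 0.8 to 1.25 as a yardstick for close to 1.

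**1. The plan's own figures.** 375 × 0.685 = 256.9 malignant, leaving 118.1 benign. Half-widths 1.96·√(p(1−p)/n) are 4.1 points (0.87, n = 257), 6.8 (0.83, n = 118), 3.3 (0.92, n = 257) and 5.4 (0.90, n = 118). All agree with the protocol, so the sample-size figures are not in question.

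**2. Decile size.** 375/10 = 37.5 patients, and 118/37.5 = 3.1. A model that sorts well therefore fills roughly the lowest three deciles with benign nodules.

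**3. Hand check.** If the mean risk in a decile is p, the chance of no cancer among 37 patients is about (1 − p)^37. The simulated mean true risk in the lowest decile is 0.002 (correlation 0.3) to 0.005 (correlation 0.6), which gives 93% and 83%.

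**4. Simulation scoring the true risks, that is, a perfect model.** The separations are 1.405 + 1.282 = 2.687 for PET and 1.126 + 0.954 = 2.081 for DCE-CT. Where two figures are shown, they come from separate simulation runs.

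| Tests | AUC | No cancer, decile 1 | No cancer, decile 2 |
|---|---|---|---|
| Both, correlation 0.3 | 0.983 | 93–94% | 37–38% |
| Both, correlation 0.5 | 0.977 | 86% | 22–24% |
| Both, correlation 0.6 | 0.974 | 82% | 16–19% |
| PET alone, 92/90 | 0.971 | 81% | 12% |
| DCE-CT alone, 87/83 | 0.929 | 28% | – |
| Weak test, 77/76 | 0.847 | 0.3% | 0% |

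The weak case takes the lowest published PET values quoted in section 9.1.

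- At correlation 0.5 the lowest decile expects 0.15 cancers. The observed count is a whole number: at 0 the ratio is undefined, and at 1 it is about 0.15. It cannot be close to 1. Decile 2 expects about 1.65 cancers and is undefined or outside 0.8–1.25 in about 80% of datasets.
- With weaker tests the ratio can be computed but scatters. Decile 1 is undefined or outside the band in 80% (DCE-CT alone) and 57% (weak test).
- At the planning accuracies the mean absolute gap between observed and expected risk is 0.4 to 0.8 percentage points in decile 1 and 2.1 to 2.7 in decile 2. Calibration is good there, and only the ratio fails to show it.
- Deciles 5 to 10 stay within 0.8–1.25 in at least 97% of datasets in every scenario.

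**5. Does the assumed correlation matter?** The squared separation of the best two-test score is (a² − 2rab + b²)/(1 − r²), with a = 2.687 and b = 2.081. It is smallest at r = b/a = 0.77, where it equals a², the PET-alone value. Within this model no correlation can bring the decile 1 figure below the PET-alone 81%.

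**6. Survival model.** Sixty datasets were fitted per scenario with 5% dropout. When tests of planning accuracy separate patients with cancer from patients who never have it, the lowest decile had no event in 98%. Under an assumed proportional-hazards truth this fell to 5%, with the decile 1 ratio undefined or outside 0.8–1.25 in 73%.

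**7. Slope against ratio.** Take true risks of 0.10, 0.50 and 0.90 and double every predicted odds. The predictions become 0.182, 0.667 and 0.947, so E/O is 1.82, 1.33 and 1.05. On the logit scale this is a constant shift, so the slope is still exactly 1. Conversely, the fitted logistic model had an apparent slope of 1 to rounding error in every simulated dataset, whatever the decile ratios did. The survival model also returned 1.000 when refitted on its own linear predictor.

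**The case against.** The case for leaving the text alone has real weight. The standard is descriptive and sets no pass mark, and 0.8–1.25 is this review's yardstick. A statistician comparing an expected risk of 0.004 with an observed 0 would see agreement. Undefined ratios depend on strong discrimination and on assumed marker distributions, and the published ranges quoted in the protocol allow weaker tests. The protocol already recognises the same-data problem and plans bootstrapping. The slope sentence could be read as the slope of decile observed on expected risk, which is not 1 by construction. Curves, intervals and empty groups are often left to a statistical analysis plan, which is not at hand here.

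Most of this limits the size of the point without removing it. The ratio is the measure the protocol names and the only one to which it attaches a standard, so this is more than an omitted detail. The zero-count problem needs no yardstick. Bootstrapping can correct a slope, but it cannot repair a ratio with zero in its denominator. On either reading of slope, the equivalence does not hold.

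Three stronger readings are tempting and are not supported:

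- *One check always fails and the other always passes.* Only the low-risk deciles fail. The slope is named only for the survival model, and optimism correction is at least contemplated there.
- *Overall E/O equals 1 by construction.* This is exact for the logistic model but only approximate for the survival model (0.986 to 1.031 in the runs above). The protocol does not propose overall E/O as a measure.
- *The faulty check drives extension of the model.* The rule in 9.1(i) begins: "If the above methods all show poor accuracy performance (in terms of calibration and/or discrimination". It needs all the methods to perform poorly, including the analyses of the tests themselves. That is unlikely at the high accuracy where undefined ratios are common. The E/O standard itself sits in 9.1(ii), which has no extension rule.

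**Conclusion.** The point holds in a limited form. At the protocol's planning accuracies, decile E/O will usually be undefined in the lowest decile (about 82 to 94% of datasets for two tests with correlation 0.3 to 0.6) and often unstable in the second and third, even when calibration is correct. With much weaker tests, empty deciles become rare but the lowest ratios still scatter widely. The upper deciles are sound. The figures rest on equal-variance normal markers; the direction does not, since it follows from about 37 patients per decile and very low risk at the bottom. The equivalence with a slope of 1 is wrong as stated, and an uncorrected slope from the development data is uninformative.

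The primary accuracy outcomes and the sample size are untouched. What is at stake is how the two prediction models are judged and reported at low predicted risk.

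**What to change.** In sections 9.1(i) and 9.1(ii):

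1. Judge calibration by a smoothed curve of outcome against predicted risk with a 95% band. For the survival model, use a version that allows for censoring at 2 years. If deciles are kept, report observed minus expected risk with a confidence interval in place of the ratio; the interval must be one that remains valid with no events.
2. Delete the sentence in 9.1(ii) that equates decile E/O with the calibration slope.
3. State that the calibration slope and calibration-in-the-large are among the quantities corrected by the bootstrap already planned, and make that correction unconditional for the survival model.

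This costs a sentence or two in each part and slightly more programming. It needs no additional data.
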